### Study population

We aim to enrol 250 patients, divided into two groups with minimum 125 patients per group: COVID group and non-COVID group. Both groups will be monitored at 6, 12 and 24 months since the first procedure visit, defined as the baseline.

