### Statistical analysis

The statistical analyses will be performed using the SPSS for Windows, version 19.0.1, R (version 3.1.2) package for statistical analysis and STATA 13. Non-normally distributed variables will be expressed as median with interquartile range and normally distributed variables as mean ± SD, as appropriate. Between-group comparisons will be assessed for nominal variables with the Chi-square test, and by Kruskal-Wallis test or one-way ANOVA for the rest of the variables. In order to comply with the assumptions for regression analysis, logarithmic conversion will be performed for non-normally distributed variables. Pearson correlation coefficient will be used to determine correlations between variables. Stepwise multivariate regression analysis including all univariate associates (*p* < 0.05) will be used to assess the independent associations between variables. Survival and time-to-event analysis of outcomes will be performed using Kaplan-Meier cumulative survival plots and Cox proportional hazards model, including adjustment for potential confounding factors. In the multivariate Cox models, we will adjust for all variables that will be correlated to the study outcomes with *P* < 0.05 at univariate Cox analyses.

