### Sample size power calculation

According to sample size power calculations, including 125 patients in each group will provide statistical power (alpha 0.05 and power 80%) for an estimated difference in the mortality rate of 9% [29] in the non-COVID group compared to 22% mortality in the COVID positive group [30–34].

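### The covariate rule for the adjusted Cox models sets no ceiling on model size, while the plan's own mortality rates give only about 39 deaths, so the adjusted COVID hazard ratio for death is at risk of overfitting if many variables pass the screen

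*Protocol article*

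**What the plan says.** The Statistical analysis section of the protocol article plans Kaplan-Meier plots and Cox models that adjust for potential confounders, none of which it names. Its selection rule for the adjusted models reads: "we will adjust for all variables that will be correlated to the study outcomes". The criterion is a P value below 0.05 in a one-variable Cox model. It states no upper limit, no fixed confounder list and no penalisation.

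The Study population section states: "We aim to enrol 250 patients, divided into two groups with minimum 125 patients per group". Follow-up is given as: "Both groups will be monitored at 6, 12 and 24 months since the first procedure visit". The Sample size power calculation section sizes the study on death alone, at "alpha 0.05 and power 80" per cent, for a "mortality rate of 9% [29] in the non-COVID group compared to 22% mortality in the COVID positive group". All-cause mortality is one of the primary outcomes in the Outcome data section. No event rate is given for the cardiovascular or renal composite.

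**The concern.** A Cox model draws its information from events, not patients. The rule lets the data decide how many covariates enter, and the pool is large. The Clinical data section names about 22 items (my count, with open-ended lists). Table 2 adds six serum biomarkers and at least eight imaging or physiological measures, so 22 + 6 + 8 = 36. Several describe the same thing: weight and body mass index, urea and creatinine, the several bioimpedance volumes, left ventricular function and strain. Correlated variables tend to pass a univariate screen together.

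With few deaths per parameter, partial-likelihood estimates drift away from a hazard ratio of 1 and model-based standard errors become too small. What is at stake is the adjusted COVID effect on mortality, the only outcome the study is sized for. It could be overstated and called significant more often than the nominal 5%.

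**Working it through.** **1. The plan's own figure.** Inputs from the sample size section: 9% and 22%, alpha 0.05 (two-sided assumed), power 80%, 125 per group. Mean proportion 0.155; difference 0.13.

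n = [1.96 × √(2 × 0.155 × 0.845) + 0.842 × √(0.09 × 0.91 + 0.22 × 0.78)]² / 0.13² = (1.003 + 0.424)² / 0.0169 ≈ 121 per group without continuity correction (136 with it). Power at 125 per group is 81.4%. The stated figure is reproduced.

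**2. Expected deaths.** 125 × 0.09 = 11.25 and 125 × 0.22 = 27.5; total 38.75. This takes the two rates as cumulative over follow-up, because no time horizon is stated. No dropout rate is given either. If 5% to 20% of the information is lost (assumed range), the total becomes 38.75 × 0.95 = 36.8 to 38.75 × 0.80 = 31.0.

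**3. Deaths per parameter** (38.75 / k, counting COVID group as a parameter): k = 4 gives 9.7; 8 gives 4.8; 10 gives 3.9; 15 gives 2.6; 20 gives 1.9; 30 gives 1.3.

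**4. Simulation of the stated rule.** Each run has 250 patients, about 39 deaths and 10 to 30 candidate covariates. Each candidate is tested in a one-variable Cox model, and those with P < 0.05 enter with COVID group. The alternative hazard ratio is the one implied by the plan: ln(0.78) / ln(0.91) = 2.63, a log hazard ratio of 0.97. Covariate effects and correlations are assumptions; the document gives none. Batches had 300 to 3,400 runs.

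| Covariates admitted | Assumed setting | COVID term at true HR 2.63 | 95% CI coverage | False positives at HR 1 (unadjusted) |
|---|---|---|---|---|
| 4–5 | 10 candidates, correlation 0.1; or 30, correlation 0 | mean log HR 1.00 or 0.93 | about 95–96% | – |
| 10–11 | 30 candidates, 12 prognostic, correlation 0.05 | median HR 2.60–2.68 | 91.5–94.4% | about 6–8% (about 4–6%) |
| 16–17 | 20 candidates, 8 prognostic, correlation 0.2 | mean log HR 1.05; mean SE 0.39, empirical SD 0.44 | about 94–95% | – |
| 18–19 | 30 candidates, correlation 0.15 | median HR 2.99–3.11 | about 91% | 7.5–8.8% (4.0–4.3%) |
| 26 | 30 candidates, 10 prognostic, correlation 0.2 | mean log HR 1.27; mean SE 0.45, empirical SD 0.58 | 87–90% | – |
| 27–28 | 30 candidates, correlation 0.3 | median HR 3.21–3.29 | 89–90% | 8.3% (–) |

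The false-positive range at 10–11 covariates needs care. A 400-run batch gave 8.5%, with Monte Carlo standard error √(0.085 × 0.915 / 400) = 1.4 points. The largest, with 3,400 runs, gave 6.3%, with standard error √(0.063 × 0.937 / 3400) = 0.4 points. The excess over the unadjusted test is real but modest.

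**The case against.** **A reader might infer that the hazard ratio will be overfitted.** The document does not support that. The outcome depends on how many variables pass, which is unknown. With 4–5 admitted the intervals behave well, and with 10–11 the estimate is not inflated. The number is not unlimited either: the collected variables and the P < 0.05 screen bound it. This objection stands, and the point is therefore conditional.

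**A reader might extend the point to all the Cox models.** The 39 events are deaths. Without rates for the cardiovascular or renal composite, no event count for them can be derived. This stands too.

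**The pool may be smaller than 36.** The preceding sentence speaks of potential confounders, and markers of cardiovascular risk and endothelial dysfunction are themselves listed as a primary outcome. The rule could be read as selecting only among confounders, and an analyst would probably drop near-duplicates. That is reasonable, but the text says all variables and defines no narrower pool.

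**Adjustment is useful.** In the setting with 10–11 covariates admitted, the unadjusted model gave about 2.23–2.30 for a conditional hazard ratio of 2.63, and the adjusted model recovered it. The point is against an uncapped model, not against adjustment.

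**Such detail belongs in the SAP.** This does not stand. The article states a complete selection rule, and a SAP that followed it would inherit the weakness.

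**Conclusion.** The concern holds in conditional form. The rule puts no ceiling on model size, and the plan's rates give about 39 deaths, which support about four parameters at ten deaths each. Ten is a convention and is not in the document; at five deaths each, 38.75 / 5 gives about seven. Distortion is slight at around ten admitted covariates. Toward twenty it becomes material in some of the assumed settings: about 91% coverage and a median near 3.0–3.1 at 18–19, but near-nominal coverage in the setting with 16–17. Close to thirty it is clear. Fewer deaths than planned would make it worse. So would complete-case fitting if an admitted variable is often missing; the limitations section expects difficulty with strain, bioimpedance and arterial stiffness in some patients.

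These sizes rest on assumed effects and correlations, and they apply to all-cause mortality only. The weakness should be corrected before analysis, but it does not undermine the design.

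**What to change.** In the between-group mortality model, replace the univariate screen with COVID group, always retained, plus a short set of pre-infection confounders fixed in advance and sized to the expected deaths. At ten per parameter that is about three further parameters (38.75 / 4 = 9.7). A fourth would give 38.75 / 5 = 7.75. Parameters, not variables, must be counted: a three-level kidney disease category uses two. Allow one variable per construct. Restrict the set to pre-infection characteristics, because the COVID group's baseline measurements come at least two weeks after the positive test.

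Two alternatives allow more confounders:

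- A propensity score built from pre-infection variables, followed by a weighted Cox model with the group term only and robust standard errors. The score model is limited by 125 versus 125 patients rather than by 39 deaths.
- Firth-penalised Cox regression with profile-likelihood intervals for any larger model.

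The cost is SAP wording and standard routines in R or Stata, both already named in the plan, with no new data. The downside is that fewer individual covariate effects are reported.

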### Sample size power calculation

According to sample size power calculations, including 125 patients in each group will provide statistical power (alpha 0.05 and power 80%) for an estimated difference in the mortality rate of 9% [29] in the non-COVID group compared to 22% mortality in the COVID positive group [30–34].

### Strengths and limitations of the study protocol

To our best knowledge, this is the first study that aims to evaluate the long-term CV risk after COVID-19 disease in CKD, dialysis or KTx patients. By using a holistic approach, this study can contribute to a better understanding of the long-COVID syndrome and can improve the risk stratification in a special population that already associates an increased CV risk.

Due to nature of the study, i.e. clinical evaluation of CKD stage 3–5, dialysis or KTx patients with a confirmed positive result for SARS-CoV-2 virus, and the lack of previous experimental work on this particular virus, we can encounter several limitations, briefly described below:patient’s refusal to continue with the trial;the impossibility of performing speckle-tracking echocardiography in all patients due to suboptimal images (poor acoustic window) or to metallic joint prostheses, cardiac stent or pacemakers, decompensated cirrhosis and limb amputation patients, due to bioimpedance technique limitations;the difficulty for the arterial stiffness assessment in obese patients.

## Discussion

Recent studies show a growing interest in long-term CV sequeale of COVID-19 and focus on a better understanding of the underlying mechanisms and possible therapeutic options.

Analysing the active clinical trials registered at Clinicaltrials.gov, regarding the post-COVID-19 syndrome manifestations, there are several found studies as presented in Table 3, at both CV and renal level, but none dealing with the purpose of this study.

**Table 3 Tab3:** Active clinical trials concerning to post- COVID-19 syndrome

Condition	Outcomes	Type	Trial identifier
COVID-19	Long-term morbidities and sequels of SARS-CoV-2 infections in the general population (NAPKON-POP)	Observational on 2000 participants (estimated)	NCT04679584, recruiting
COVID-19, Cardiac Disease	Sequelae (organ dysfunction) after COVID-19 (12 months)	Observational on 120 participants (estimated)	NCT04442789, recruiting
COVID-19, Hypertension	Average 24 hour Ambulatory Blood Pressure Monitoring - Systolic Blood Pressure, (all day and night) at 12 months in SARS-CoV-2 cases	Observational on 150 participants (estimated)	NCT05087290, recruiting
COVID-19	Native myocardial T1 relaxation time (MRI) at 12 weeks post COVID-19 diagnosis	Observational on 215 participants (actual enrolment)	NCT04525404, active, not recruiting
COVID-19	Presence of at least one clinical, biological and/or imaging cardiovascular anomaly within 1 month of recovering	Observational on 200 participants (estimated)	NCT04452630, recruiting
COVID-19	Incidence of major cardiovascular events (congestive heart failure, myocardial infarction, cardiomyopathy and ischemic stroke) and of atrial arrhythmia, 12 months post-COVID-19	Observational (Patient Registry) on 100 participants (estimated)	NCT04605965, recruiting
COVID-19	Echocardiographic strain measurements of the left, right heart and vascular ultrasound findings up to 12 months	Observational on 250 participants (estimated)	NCT04756193, recruiting
COVID-19, ARDS	Evaluation of evolution of renal and right and left myocardic functions during first year after ICU discharged in population studied	Observational on 150 participants (estimated)	NCT04401111, recruiting
COVID-19, AKI	GFR loss at 6 months post-hospital admission, Cystatin C as indicator of mortality, respiratory illness and disease severity at 30 days post-hospital admission	Observational (Patient Registry) on 900 participants (estimated)	NCT04353583, recruiting
COVID-19, Kidney Transplant	Predictive value of IL-6 contents of whole blood samples after ex vivo stimulation with LPS and ATP over 10 months	Interventional (Clinical Trial) on 115 participants (estimated)	NCT04369456, recruiting
COVID-19, AKI, CKD, ESRD, Transplant, Failure, Kidney	AKI incidence from hospital admission through hospital discharge up to 24 weeks, dialysis requirement through study completion up to 1 year from enrolment, hospital mortality within 1 year, renal functional recovery assessed at 3, 6 and 12 months from enrolment at hospital admission	Observational on 2000 participants (estimated)	NCT04491227, Enrolling by invitation

The comprehensive review of Nalbandian et al. [21] describes based on available current literature on post-acute COVID-19 syndrome, the most persistent symptoms and/or long-term complications beyond 4 weeks from the start SARS-CoV-2 replication. Briefly, besides, the usual fatigue, decline in quality of life, muscular weakness and pain, the authors put together an organ-specific complications of post-acute COVID-19. At CV level, the authors included palpitations, dyspnea and chest pain as symptoms, along with increased cardiometabolic demand, myocardial fibrosis or scarring, arrhythmias, tachycardia and autonomic dysfunction. At renal level, reduced eGFR has been reported at 6 months follow-up and persistent impaired renal function.

MRI studies indicate that myocardial inflammation persists more than 2 months after the resolution of the acute episode [35] and myocardial injury can occur even in previously healthy subjects with mild or asymptomatic forms of COVID-19 [36]. Myocardial inflammation can lead to fibrotic remodelling which in turn manifests through alteration of cardiac relaxation. In 48 patients that were evaluated by transthoracic echocardiography at 6 months distance from COVID-19, myocardial injury identified by elevations in cardiac troponin during the acute phase was significantly associated with diastolic dysfunction, but this abnormality was revealed only after mild exercise. Systolic left ventricle and right ventricular functions were normal, and there were no significant valvulopathies or pericardial disease [37].

Compared with controls, in patients with COVID-19, both left ventricular (ejection fraction, GLS) and right ventricular systolic function (TAPSE, RVLS) are significantly reduced when compared to controls and independently associated with higher mortality rates [38–41]. RVFWS is altered even in mild forms of COVID-19 and not necessarily in the presence of biomarkers indicating myocardial injury. However, RVFWS is more impaired in those with biochemical evidence of myocardial injury and is directly correlated with the disease severity [42]. Studies regarding the prognostic role of right ventricular fractional area change (RVFAC) have contradictory results, as this parameter is inconsistently associated with mortality rate [42]. Right ventricular diameter was also correlated with mortality rates [40, 43]. Most studies suggest that both right ventricular and left ventricular function improve at follow-up [42, 44], although there is also data that indicate that left ventricular function can remain impaired [44]. IL-6 levels could predict right ventricular systolic dysfunction in patients with COVID-19 [45].

LUS is a widely used investigation that can describe lung parenchymal abnormalities by identifying B-lines, B-line like artefacts, consolidation or pleural line irregularities. The presence of B-lines was significantly correlated with disease severity and longer duration of symptoms, as well as with increased mortality [46]. Moreover, LUS has practical application in documenting pulmonary sequelae in patients with severe COVID-19 pneumonia and can predict its progression [47].

FMD is a widely recognized indicator of both subclinical atherosclerosis and coronary artery endothelial function [48], with important prognostic value [49]. Compared with healthy controls, significantly lower FMD values were reported during the acute phase of COVID-19 [50, 51]. In addition, FMD was an independent predictor of mortality in this setting [51, 52]. FMD was also assessed in the post-COVID population, with evidence suggesting the persistence of impaired FMD at 3 months distance after the acute event [53]. In a study that included 133 convalescent moderate-to-severe COVID-19 patients and 133 matched controls, FMD values were significantly lower within 2 months from COVID-19, and were directly correlated with the severity of pulmonary disease. However, this difference was nullified by female gender, smoking or the presence of more than 3 concomitant risk factors [54]. Thus, one can conclude that COVID-19 is an independent predictor of ED [55]. Interestingly, pulmonary rehabilitation increased FMD with ~ 2% among 82 patients with a history of severe or critical COVID-19 [56].

Arterial stiffness is a risk factor for in-hospital mortality in COVID-19 patients [57] and also for increased hospitalization duration [58]. PWV is also increased in patients with prior COVID-19 disease [59, 60].

The up-to-date review of Samprathi and Jayashree [61] presents the rational use of available biomarkers in the diagnosis and management of patients with COVID-19. The authors discuss based on Sars-CoV-2 pathophysiology, the laboratory tests offered to the clinician, from hematological, inflammatory, coagulative and biochemical parameters and up to cardiac biomarkers. The combined hematological biomarkers, namely increased leukocytes, neutrophils, CRP, PCT and ferritin, cytokine levels (IL-2R, IL-6, IL-8, IL-10 and TNF-α) and decreased lymphocyte counts predicts the severity of the disease and hospital admission. At inflammatory level, elevated CRP, PCT, cytokines (IL-6, IL-1b, IL-2, IL-8, IL-17, G-CSF, GMCSF, IP-10, MCP-1, CCL3, and TNFα) values forecast also, predicts progression to severe disease. Raised cardiac biomarkers involving CK, CK-MB, LDH, Mb, cTnI, α-HBDH, AST, and NT-proBNP were observed especially in severe illness and were associated with higher mortality. The proposed biomarkers play an essential role in early suspicion, diagnosis, monitoring, and recognition of acute complications, but what about on the long-term effects of COVID-19?

In July 2021, Andrianto et al. [62] conducted a literature search for observational studies that analysed the relationship between ED biomarkers and clinical outcomes in COVID-19 patients. In a meta-analysis that included 1187 patients from 17 studies, VWF antigen, PAI-1, t-PA, sTM were predictors of worse outcome in COVID-19 patients. The elevated biomarkers that display an endothelial dysfunction in COVID-19 increase also the risk of vascular complications, poor outcomes, and death.

Overall, we can disclose that since COVID-19 is not a simple upper respiratory tract disease, and more a multisystemic one that affects many organs, it generates long-term permanent sequelae with a serious burden on individuals and the health systems in the near future.

## Data Availability

The datasets used and/or analysed during the current study are available from the corresponding author on reasonable request, namely [name] at [contact].

## Abbreviations

ACE-2: Angiotensin-converting enzyme 2
ADMA: Asymmetric dimethylarginine
AFO: Absolute fluid overload
AHA: American Heart Association
α-HBDH: Alpha-hydroxybutyrate dehydrogenase
AKI: Acute kidney injury
AST: Aspartate aminotransferase
BIS: Bioimpedance spectroscopy
CCL3: Macrophage inflammatory protein-1 α
CK: Creatine kinase
CKD: Chronic kidney disease
CK-MB: Creatine kinase-myocardial bound
COVID-19: Coronavirus disease 2019
CRP: C-reactive protein
cTnI: Cardiac troponin I
CV: Cardiovascular
CVD: Cardiovascular disease
ECW: Extracellular water
ED: Endothelial dysfunction
eGFR: Estimated Glomerular Filtration Rate
ELISA: Enzyme linked immunosorbent assay
ERA-EDTA: European Renal Association- European Dialysis and Transplant Association
ESKD: End stage kidney disease
FMD: Flow-mediated dilation
G-CSF: Granulocyte colony-stimulating factor
GMCSF: Granulocyte-macrophage colony-stimulating factor
ICAM-1: Intercellular Adhesion Molecule 1
ICW: Intracellular water
IL-: Interleukin-
IP-10: Interferon gamma-induced protein 10
KTx: Kidney transplant
LDH: Lactate dehydrogenase
LUS: Lung ultrasonography
LVGLS: Left ventricular global longitudinal strain
Mb: Myoglobin
MCP-1: Monocyte chemoattractant protein-1
MRI: Magnetic resonance imaging
NO: Nitric oxide
NT-proBNP: N-terminal pro b-type natriuretic peptide
PAI-1: Plasminogen activator inhibitor-1 antigen
PCT: Procalcitonin
PWV: Pulse wave velocity
RFO: Relative fluid overload
RNA: Ribonucleic acid
RT-PCR: Reverse transcriptase polymerase chain reaction
RVFWS: Right ventricular free wall strain
RVFAC: Right ventricular fractional area change
RVLS: Right ventricular systolic function
SARS-CoV-2: Severe acute respiratory syndrome coronavirus-2
sTM: Soluble thrombomodulin
TAPSE: Tricuspid annular plane systolic excursion
TBW: Total body water
TNF-α: Tumor necrosis factor α
t-PA: Tissue-type plasminogen activator
VCAM-1: Vascular cell adhesion molecule 1
VWF: von Willebrand factor
WHO: World Health Organization
